#### Multivariate analysis

##### Analysis for the secondary endpoints

For the secondary endpoints, the following analyses will be performed:Anatomic results based on OCT scan (absence of SRF versus persistent SRF) at evaluation point 1 will be compared to the baseline.Number of subsequent treatments needed in each treatment arm.Mean change from baseline in ETDRS BCVA in the study eye at 6 to 8 weeks after treatment and at the end evaluation will be compared between the two treatment modalities.Mean change from evaluation point 1 in ETDRS BCVA in the study eye at final evaluation among those with subsequent and those without subsequent treatment will be compared between the two treatment modalitiesMean change from baseline in retinal sensitivity in the study eye to 6 to 8 weeks after treatment will be compared between the two treatment modalities.Mean change from baseline in the NEI-VFQ-25 questionnaire to 6 to 8 weeks after treatment will be compared among the two treatment modalities.

The first two analyses will be performed by the use of a cross-table. Furthermore, the continuous secondary variables will be analyzed using an ANCOVA model with baseline as and treatment as factor. For categorical secondary endpoints, a chi-square test will be performed. In addition, a logistic model with baseline as covariate and treatment as factor will be performed. The change from baseline in the NEI-VFQ-25 questionnaire results will be summarized descriptively.

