
**Fig. 1 Fig1:**
[figure not shown]
Multimodal imaging in chronic central serous chorioretinopathy. Examples of fluorescein angiography (FA), indocyanine green (ICG) angiography and spectral-domain optical coherence tomography (SD-OCT) in chronic central serous chorioretinopathy (cCSC). (**a-c**) Right eye of a patient with cCSC with more widespread leakage on FA (**a**) corresponding with hyperfluorescent areas on ICG angiography (**b**) and SRF on SD-OCT (**c**)

A prolonged neuroretinal detachment in the macula leads to progressive and permanent central visual loss due to photoreceptor atrophy. In addition, Piccolino et al. described the occurrence of not only SRF, but also of intraretinal fluid accumulations, posterior cystoid degeneration, and prolonged neuroretinal detachments in severe cCSC cases [17]. Nicolo et al. have shown that this posterior cystoid degeneration is associated with a poorer response to photodynamic therapy (PDT) [17, 18]. A loss of visual acuity with image distortion and a loss of color and contrast vision may have a significant impact on a patient’s personal and professional life. Early diagnosis and treatment is important to try to improve the visual outcome and quality of life, as long-term follow-up studies have shown that the natural course of cCSC often results in permanent visual loss [3, 9, 10, 19–25]. Therefore, several treatment options have emerged in an attempt to accelerate the resolution of SRF accumulation and to improve the visual outcome in patients with cCSC. Treatment within 4 months after the onset of the disease has been advocated by several authors, based on the observation that permanent visual loss may result from prolonged duration of disease [2, 3]. Photoreceptor atrophy in the fovea may occur, even after successful reattachment of the retina, after a duration of symptoms of approximately 4 months [9]. To date there is no international consensus on the optimal treatment protocol of cCSC.

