### Outline of proposed clinical trial

The PLACE study is a superiority study because retrospective studies suggest that the rate of anatomical and functional success of PDT treatment might be higher than the success of HSML treatment. Therefore, a half-dose PDT treatment arm is challenged against a treatment arm of HSML treatment.

In this study, we want to define treatment success not only on the basis of structural parameters (anatomic success, for example, the absence of SRF after treatment), but also based on functional vision-related endpoints, which are most important from a patient’s perspective. These functional vision-related endpoints will include best-corrected visual acuity (BCVA), retinal sensitivity on microperimetry and score on a validated visual function questionnaire (the NEI-VFQ-25 questionnaire) http://www.psy.cmu.edu/~scohen/ [52].

With the results of this study, we hope to establish a strong scientific foundation for further research on the optimal treatment of patients with cCSC to improve the visual outcome and quality of life of this relatively frequently occurring eye disease.

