### Trial participants

#### Overall description of the trial participants

This study will enroll subjects with cCSC with active leakage of fluid under the retina as evidenced on OCT scanning and further supported by findings on fluorescein angiography and ICG angiography, in at least one eye. If both eyes are eligible, then the eye with the longer duration of disease will be used as the study eye, except in cases where the disease is present for more than 18 months. In the latter case, which is an exclusion criterion, the other eye will be eligible for inclusion if the disease has been active for less than 18 months. If the nonstudy eye also has active disease, the choice to treat and the type of treatment in this eye may be chosen freely at the discretion of the responsible ophthalmologist.

Before enrolment, each subject must meet all of the following inclusion criteria and none of the exclusion criteria and agree to comply with the study requirements, including completion of all of the study visits.

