#### Inclusion criteria

The inclusion criteria are as follows:Male and female patients ≥18 years of age who are able to give written informed consent.Active cCSC.Subjective visual loss >6 weeks, interpreted as onset of active disease.SRF that includes the fovea on OCT scanning at baseline examination. *Note*: SRF does *no**t* have to include fovea on OCT to be eligible for treatment at control visit 1 as long as there is persistent SRF in the macula, which is interpreted as persistently active disease.Hyperfluorescent areas on ICG angiography.≥ 1 ill-defined hyperfluorescent leakage areas on fluorescein angiography with RPE window defect(s) that are compatible with cCSC.

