#### Exclusion criteria

The participant may not enter the study if any of the following apply:Any previous treatments for active CSC in the study eye.Current treatment with corticosteroids (topical or systemic), corticosteroid use within 3 months before the possible start of trial treatment, or anticipated start of corticosteroid treatment within the first 7 to 8 months from the start of the trial period.Evidence of other diagnosis that can explain serous SRF or visual loss.BCVA <20/200 (Snellen equivalent).Profound chorioretinal atrophy in central macular area on ophthalmoscopy and OCT.Myopia >6D.Visual loss and/or serous detachment on OCT <6 weeks.Continuous and/or progressive visual loss >18 months or serous detachment on OCT >18 months.No hyperfluorescence on ICG angiography.Intraretinal edema on OCT.Contraindications (relative) for PDT treatment (pregnancy, porphyria, severely disturbed liver function). Pregnancy will not be routinely tested in female patients, but the possibility of pregnancy will be discussed during eligibility screening.Contraindications (relative) for fluorescein angiography or ICG angiography (known allergies especially against shellfish, previous reactions).Soft drusen in treated eye or fellow eye, signs of choroidal neovascularization on ophthalmoscopy and/or fluorescein angiography/ICG angiography.

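### The BCVA and retinal-sensitivity models leave out symptom duration, a pre-randomisation factor the protocol links to permanent visual loss; adding it would be a cheap but modest and uncertain gain in precision

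*Protocol article*

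**What the plan says.** The section Analysis for the secondary endpoints states that "the continuous secondary variables will be analyzed using an ANCOVA model with baseline as and treatment as factor". A word is missing after the first 'as'. The parallel sentence for categorical endpoints, "a logistic model with baseline as covariate and treatment as factor will be performed", shows that 'covariate' is meant. No other term is named in either model.

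The Background section on chronic central serous chorioretinopathy says: "Photoreceptor atrophy in the fovea may occur, even after successful reattachment of the retina, after a duration of symptoms of approximately 4 months".

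Three entry rules depend on duration:
- Inclusion criteria: "Subjective visual loss >6 weeks, interpreted as onset of active disease".
- Exclusion criteria: "Continuous and/or progressive visual loss >18 months or serous detachment on OCT >18 months".
- Overall description of the trial participants, where both eyes qualify: "the eye with the longer duration of disease will be used as the study eye".

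The Randomization section describes block randomisation without minimisation and names no stratification by duration. The Outline of proposed clinical trial calls the functional endpoints the ones that matter most to patients.

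The point applies most clearly to BCVA and microperimetry. NEI-VFQ-25 is listed among the comparisons between arms, but the same section also says: "The change from baseline in the NEI-VFQ-25 questionnaire results will be summarized descriptively".

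**The concern.** By the protocol's own account, duration bears on how much vision can still be recovered, and the entry window covers both sides of the 4-month point named in the Background. Baseline letters need not show this fully. A low score may reflect fluid that can resolve or photoreceptor loss that cannot, so two eyes with the same baseline acuity and very different durations may have different prospects.

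If duration predicts the functional change once the baseline value is in the model, leaving it out puts explainable variation into the error term. What is at stake is the width of the confidence intervals for BCVA and retinal sensitivity. The primary endpoint and the logistic models concern resolution of fluid and are not part of this point.

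**Working it through.** **The plan's own figure.** The only sample size given (Number of participants) is for the binary primary endpoint. With pooled variance, two-sided α 0.05, power 80% and no continuity correction, n per arm = [1.96·√(2p̄(1−p̄)) + 0.842·√(p₁(1−p₁)+p₂(1−p₂))]² / (p₁−p₂)².
- 50% v 80%: 39 (stated 40).
- 50% v 72%: 76. Multiplying by 1.008, a standard inflation factor for one O'Brien-Fleming look that is not in the document, gives 77 (stated 78). The 50%/72% pair is my reading of the 22-point difference.

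Both reproduce within two patients. They say nothing about the functional endpoints, for which no power or precision is stated.

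**Inputs for the functional endpoints.** From the document: 78 per arm; duration from above 6 weeks (taken as 1.5 months) to 18 months. Assumed, because the document gives none of them: log-duration uniform over that range; SD 7 letters around the model that includes duration; true arm difference 3 letters; slope 1.5, 2.5 or 3.5 letters lost per log-unit of duration.

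**Variance explained.** The log range is ln(18/1.5) = 2.485, so Var(log-duration) = 2.485²/12 = 0.515 (SD 0.717). Then R² = b²·0.515 / (7² + b²·0.515). The equivalent gain in patients is 156·(1/(1−R²) − 1), and the narrowing of the confidence interval is 1 − √(1−R²).

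| Slope b | R² | Equivalent extra patients | CI narrower by | Power without duration | Power with duration |
|---|---|---|---|---|---|
| 1.5 | 1.16/50.16 = 2.3% | 3.7 | 1.2% | 74.8% | 75.5% |
| 2.5 | 3.22/52.22 = 6.2% | 10.2 | 3.1% | 73.1% | 75.5% |
| 3.5 | 6.30/55.30 = 11.4% | 20.1 | 5.9% | 70.7% | 75.5% |

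Power comes from the noncentral t distribution. The standard error is √(49 + b²·0.515)·√(2/78) without duration (153 df) and 7·√(2/78)·√(153/152) with it (152 df, with the cost of the extra term included). The gains are 0.7, 2.4 and 4.9 points. The adjusted power is the same in every row because the residual SD is held at 7.

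**The same question without assuming letters.** Let r be the partial correlation of duration with outcome, given baseline and arm. The residual variance falls by the factor 1 − r². Take a difference that has 80% power at 78 per arm, which is 2.80·√(2/78) = 0.449 residual SD:

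| r | Variance reduction | Equivalent n per arm | Power |
|---|---|---|---|
| 0.1 | 1% | 79 | 80.4% |
| 0.2 | 4% | 81 | 81.6% |
| 0.3 | 9% | 86 | 83.6% |
| 0.4 | 16% | 93 | 86.4% |
| 0.5 | 25% | 104 | 89.9% |

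The lost degree of freedom costs a factor 153/152, about 0.7%. There is a net gain once r² exceeds 1/153, that is once |r| is above about 0.08.

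**Chance imbalance.** The between-arm difference in mean log-duration has SD 0.717·√(2/78) = 0.115. Times the slope, it moves the unadjusted estimate by an SD of 0.17, 0.29 or 0.40 letters. The unadjusted standard error is 1.13 to 1.19 letters and already includes this variation.

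**The case against.** The strongest reply is that nothing here is stated wrongly. ANCOVA on the baseline value is conventional, and the baseline value is usually the strongest predictor available. Further covariates are often left to an analysis plan, and an incomplete sentence is weak evidence that the list of covariates is closed. This stands as far as it denies an error. It does not remove the point, because the article does state a model and its terms can be assessed.

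A second reply is that the size is entirely assumed. That is correct. The Background says atrophy may occur; it does not say that duration predicts change once baseline function is known. Atrophy present at entry would show at least partly in baseline BCVA and microperimetry. The exclusions (profound central atrophy, acuity below 20/200, intraretinal edema, more than 18 months) trim the range further. A small gain is more plausible than a large one.

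Two stronger readings are tempting and are not supported:
- A reader might infer that a chance imbalance in duration distorts the functional comparison. Under randomisation the planned analysis is unbiased, the likely shift is a fraction of a letter, and the standard error already covers it, so the type I error is unaffected.
- A reader might infer that an onset date is already recorded. The list of collected information under Identification of potential participants names none. Eligibility needs only threshold judgements, plus a ranking when both eyes qualify. The exclusion criterion uses two clocks, visual loss and detachment on OCT. Duration must be ascertained, but the text does not show that it is captured as a number.

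**Conclusion.** The point holds as a modest efficiency improvement. The stated model for BCVA and retinal sensitivity is valid and unbiased, but it does not use a pre-randomisation factor that the protocol itself ties to permanent visual loss. Under the assumptions above, duration explains about 2% to 11% of the residual variance, worth about 4 to 20 patients or about 1 to 5 points of power. If baseline function already carries the effect, the gain is close to nil, and the most that is lost is one degree of freedom. The slopes, the SD and the 3-letter difference are assumptions; the document supplies only the sample size and the duration range. The documents do not support calling the planned analysis wrong. Priority is minor and optional.

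**What to change.** Complete the sentence under Analysis for the secondary endpoints so that, for BCVA and retinal sensitivity, the covariates are the baseline value of the endpoint and the study eye's symptom duration at randomisation, with treatment as factor. Define duration on one clock, for example from the onset of subjective visual loss used in the inclusion criteria, and state its form in advance. A log transform is one reasonable choice; the document does not dictate it. Add the duration to the CRF. The trial is open-label, so the term should be fixed before outcome data are examined.

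The cost is one sentence, one CRF field and one degree of freedom. Patient-reported onset is imprecise, which shrinks the gain but does not bias the randomised comparison.

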#### Retreatment criteria and considerations

At evaluation visit 1, at 6 to 8 weeks after treatment, an OCT scan of the retina will be performed, among other imaging examinations. If there still is SRF present in the macular area, a second treatment will be performed according to the protocol within 3 weeks after evaluation visit 1.

This second treatment (either half-dose PDT or HSML treatment) will again be guided by the hyperfluorescent area(s) on the ICG angiography that correspond(s) to SRF accumulation in the macula on the OCT scan and the hyperfluorescent “hot spots” on the midphase (approximately 3 minutes) fluorescein angiogram.

In cases where there is no more SRF under the fovea but there is persistent fluid within the macular area encircled by the optic disc and temporal retinal vascular arcade, retreatment will be performed. The rationale behind this second treatment is that the persistent fluid may be interpreted as an incomplete treatment response because SRF accumulation indicates ongoing disease activity due to choroidal vascular hyperpermeability and fluid leakage through the RPE.

Note that if a patient did not require retreatment at evaluation visit 1 (=6-8 weeks after treatment visit 1) according to the protocol but returns with visual symptoms in the period between evaluation visit 1 and the follow-up visit at 7 to 8 months, a regular clinical examination should be performed that includes at least a measurement of visual acuity, ophthalmoscopy, and OCT scan to determine whether SRF has reoccurred. If there is evidence of recurrence of SRF on OCT (and therefore disease activity), these findings should be noted in the CRF. In these cases, additional evaluations compatible with evaluation visit 2 should be performed, and the patient should be planned for treatment visit 2 (max. 2 to 3 weeks after evaluation visit 2). Further evaluation will adhere to the retreatment criteria described above.

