### Description of statistical methods

#### Univariate analysis

##### *Analysis for the primary endpoint*

The purpose of this study is to identify the difference between the efficacy of the two treatment modalities based on the anatomical effect on OCT scan (absence of SRF versus still SRF visible). As we expect one treatment to be superior to the other, this study is designed to be a superiority study. Statistical analysis on the primary parameter will be performed by analyzing the relative risk by using a cross-table comparing evaluation at 6 to 8 weeks after treatment with baseline.

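### Read as each endpoint's own baseline value, the logistic model's baseline covariate is the same for every study eye, so the planned adjustment does nothing; the cost is some precision, not bias

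*Protocol article*

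**What the plan says.** In the protocol article, the section Analysis for the secondary endpoints lists two categorical items. The first is "Anatomic results based on OCT scan (absence of SRF versus persistent SRF) at evaluation point 1 will be compared to the baseline". The second is "Number of subsequent treatments needed in each treatment arm". Categorical endpoints get a chi-square test and, in addition, "a logistic model with baseline as covariate and treatment as factor will be performed". The sentence on continuous endpoints is parallel, although a word has dropped out of it: "the continuous secondary variables will be analyzed using an ANCOVA model with baseline as and treatment as factor". Neither sentence defines baseline further.

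Two eligibility rules bear on this. Inclusion criteria requires "SRF that includes the fovea on OCT scanning at baseline examination". Exclusion criteria rules out "Any previous treatments for active CSC in the study eye".

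For the primary endpoint, "Statistical analysis on the primary parameter will be performed by analyzing the relative risk by using a cross-table", and that table is described as setting the 6-to-8-week evaluation against baseline. The section Interim analysis repeats the description.

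**The concern.** A covariate can adjust a treatment comparison only if it differs between patients. In the ANCOVA, baseline is plainly the starting value of visual acuity or retinal sensitivity, which varies. Carried over to the categorical endpoints, it becomes SRF status at entry or the number of earlier treatments, and eligibility fixes both. The only covariate-adjusted model the article plans for SRF resolution would then adjust for nothing.

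Two things are at stake. A model listed under the heading Multivariate analysis adds nothing to the chi-square test. And no analysis of SRF resolution uses baseline data that do vary, although ETDRS visual acuity and a Spectralis OCT are both obtained at baseline.

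**Working it through.** **1. The plan's own sample size (Number of participants).** The formula is the two-proportion one with pooled variance under the null hypothesis, two-sided 0.05, 80% power:

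n = [1.960·√(2p̄q̄) + 0.842·√(p₁q₁ + p₂q₂)]² / (p₁ − p₂)².

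- 80% vs 50%: n = 39 per arm. The article states 40.
- 22 points, taken as 72% vs 50% (the article does not state the pair): n = 76. Multiplying by about 1.008, an assumed factor for one O'Brien-Fleming interim look, gives 77. The article states 78.

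The stated numbers therefore reproduce to within one patient per arm, and they match an unadjusted comparison of two proportions.

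**2. Baseline value of each categorical endpoint.**

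| Endpoint | Own baseline value | Fixed by |
|---|---|---|
| SRF absent or persistent at evaluation 1 | present in all 156 eyes | Inclusion criteria |
| Subsequent treatment needed | no earlier treatment in all 156 eyes | Exclusion criteria |
| SRF absent at 7 to 8 months after initial success (listed under Secondary endpoints) | present in every eye | Inclusion criteria |

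The second row is closely tied to the first, because the retreatment section says: "If there still is SRF present in the macular area, a second treatment will be performed according to the protocol".

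**3. What the stated model then fits.** The design columns are intercept, treatment and a constant. The matrix has rank 2 out of 3, so the covariate's coefficient cannot be estimated. Once it is dropped, the unadjusted model remains. For a table at the planning rates, 56/78 vs 39/78:

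- log odds ratio = ln[(56/22)/(39/39)] = 0.934, odds ratio 2.55
- SE = √(1/56 + 1/22 + 1/39 + 1/39) = 0.339
- z = 0.934/0.339 = 2.76, p = 0.006

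These are the unadjusted figures. Reduction in variance from the adjustment: 0%.

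**4. The primary cross-table.** Relative risk = (56/78)/(39/78) = 56/39 = 1.44. It depends only on arm and SRF status at 6 to 8 weeks. Every baseline entry is SRF present, so the comparison with baseline contributes nothing to it.

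**5. What a varying covariate could add.** These are simulations with 78 per arm, 50% vs 72%, two-sided 0.05 and one standardised baseline covariate. Its strength is an assumption. Two independent simulations are shown; the first used 2,000 trials per setting.

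| Odds ratio per SD | Correlation with outcome | Simulation 1, unadjusted → adjusted | Simulation 2, unadjusted → adjusted |
|---|---|---|---|
| 1.0 | 0 | 81.7% → 81.4% | not quoted |
| 1.5 | about 0.19 | 80.5% → 81.8% | about 81% → 82% |
| 2.0 | about 0.30 | 82.0% → 84.8% | about 81% → 85% |
| 2.5 | about 0.37 | 80.7% → 84.9% | about 81% → 87% |

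The gain is about 1 to 6 points. The Monte Carlo standard error of one figure in simulation 1 is √(0.81·0.19/2000) ≈ 0.9 points, so the 4 and 6 points in the last row should not be read as a firm difference. The standardised risk difference had the same power as the logistic test, with type I error near 5%.

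**The case against.** The strongest reply is that baseline is undefined, not shown to be constant. The number of subsequent treatments has no natural baseline, and the value of zero is inferred from an exclusion criterion. The sentence on continuous endpoints is visibly garbled, the article condenses a fuller protocol, and an analysis plan that is not shown may name a varying covariate such as visual acuity. This stands as a caveat: the point rests on the natural reading of parallel sentences. If another variable was meant, naming it settles the matter.

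Second, an unadjusted relative risk in a 1:1 randomised trial is valid, and the sample size was built for it. This stands in full. A reader might infer that the primary analysis is biased or wrong because it ignores baseline; nothing in the article supports that. Type I error is unaffected, and the logistic model is an additional secondary analysis on which the primary conclusion does not rest.

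Third, a reader might expect a large gain in power. A gain of 9 to 10 points appears only at a correlation of 0.5, which needs an odds ratio of about 4 per SD. The article gives no prognostic strength, so that is an upper scenario and not an expected gain.

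Fourth, a reader might fear that the model will be reported as adjusted when it is not. That is conjecture: software will drop the term or the fit will fail, and the analyst will see it.

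**Conclusion.** The point holds in limited form. On the natural reading, the logistic model for the categorical endpoints adjusts for a constant and only repeats the unadjusted comparison. The comparison with baseline in the primary and interim cross-tables carries no information either. The consequence is lost precision, not bias.

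Its size depends on assumptions outside the document: 50% vs 72% success, and an odds ratio of 1.5 to 2.5 per SD (correlation about 0.2 to 0.4) for the baseline value. Under these, the forgone power is about 1 to 6 points on a base of roughly 81%. If the covariate is not prognostic, essentially nothing is gained or lost. Severity is minor to moderate, chiefly because the model as worded cannot do what it says.

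**What to change.** 1. In Analysis for the secondary endpoints, replace baseline for the categorical endpoints with a named, prespecified baseline value that varies between eyes: ETDRS visual acuity, and SRF height if it is read from the baseline OCT on file. The ANCOVA for continuous endpoints needs only its missing word restored.
2. Use this treatment-plus-covariate model for the between-arm SRF comparison at 6 to 8 weeks. Report the standardised relative risk and risk difference with 95% confidence intervals beside the unadjusted table, and state in advance which of the two carries the primary test.
3. In Analysis for the primary endpoint and in Interim analysis, describe the cross-table as treatment arm by SRF status at 6 to 8 weeks.

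The cost is wording, slightly more programming and explanation than a 2×2 table, and one measurement per stored OCT if SRF height is used. No extra patients or visits are needed. Naming the covariate beforehand also prevents its being chosen after the data are seen, which matters in an open-label trial.
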